### 9.0 DATA COLLECTION AND MANAGEMENT

### 9.1. Data management:

All clinical data will be recorded onto standardised case record forms by study clinicians. Laboratory data will be recorded in a laboratory record book by the study laboratory technicians and then transferred to the case record forms by the study co-ordinator, who will review the case record forms frequently for completeness and accuracy. Data will be transferred from the case record forms into a computerised database (EPI INFO 6.04 or Access) by data entry personnel and will be double entered to verify accuracy of entry. Two back-up files of the database will be stored on zip discs after each data entry session. For quality control, check programs will be written into the database to limit the entry of incorrect data and ensure entry of data into required fields.

### 9.2. Data quality assurance and monitoring:

All members of the study team will be educated in the study protocol prior to the onset of the trial. Knowledge of the study protocol and procedures will be assessed and documented with a post-training questionnaire. The study clinicians will complete case record forms at each patient visit. These forms will be reviewed by the study co-ordinator for completeness and accuracy. For quality control of thick blood smear slide readings, an expert microscopists who will be blinded to the patient’s treatment group will review a random sample of approximately 10% of slides. A set of standard slides with known parasite densities will be sent through the laboratory periodically to ensure continued accuracy. Study group meetings will be conducted by the co-ordinator once a week to assess progress of the study, address any difficulties, and provide performance feedback to the members of the study group. In addition members from the core facility will make regular visits to active study sites as needed.

### 9.3. Records:

Case record forms will be provided for each subject. Participants will be identified by their names and study identification number on the case record form. Patient names will not be entered into the computerised database. All patient record forms will be kept in individual files in a secure filing cabinet in the study clinic. All corrections will be made on case record forms by striking through the incorrect entry with a single line and entering the correct information adjacent to it. The correction will be initialled and dated by the investigator. Any requested information that is not obtained as specified in the protocol will have an explanation noted on the case record form as to why the required information was not obtained. Additional records will be kept in the clinical and laboratory record books that will be stored in the central study laboratory in Makerere University Medical School. The investigators will allow all requested monitoring visits, audits or reviews.

# **9.4. Use of filter paper samples**: Blood samples will be collected from the patients enrolled in the clinical study on days 0, 3, 7, 14, 21, 28 and on any unscheduled day when the patient presents with clinical deterioration or recurrent fever. Blood will be placed onto filter paper in approximately 25 ul aliquots per blood spot (4 blood spots per sample). The samples will be labeled, air-dried and stored in small, sealed sample bags at ambient temperature. Parasite DNA will subsequently be removed from the filter paper and prepared for molecular analysis using a chelex extraction method. Two types of molecular studies of the parasites collected during this clinical study are planned: 1) Genotyping of parasites collected at baseline (day 0) and during follow-up to distinguish between true recrudescence and reinfection with new parasites. Analysis will be done using a nested PCR technique targeting polymorphisms in MSP-1, MSP-2, and GLURP parasite genes to assess for molecular markers of drug resistance. 2) Analysis of polymorphisms in parasite DHFR/DHPS genes will be done using a nested PCR technique to assess for key mutations associated with SP resistance. 3) Analysis for polymorphisms in the pfcrt and pfmdr-1 genes will be done to assess for mutations associated with 4-aminoquinoline (CQ and AQ) resistance. This laboratory work will be conducted in the UCSF laboratory directed by [name] and in the Makerere University laboratory directed by [name].

### 10.0 PROTECTION OF HUMAN SUBJECTS

### 10.1. Institutional Review Board (IRB) review and informed consent:

This protocol and the informed consent documents, including any additional educational or recruitment material will be reviewed and approved by the Uganda National Council of Science and Technology (UNCST), the UCSF Committee for Human Research, and the UC Berkeley IRB before beginning the trial. Any amendments or modifications to this material will also be reviewed and approved by the IRB prior to implementation.

### 10.2. Evaluation of benefits and risks/discomforts:

Benefits that patients are likely to receive from participation in the study include enhanced medical attention, prompt diagnosis, free treatment, and close follow-up. Potential risks include drug side effects (described with chemoprophylactic use of AQ and SP) including hepatotoxicity, agranulocytosis, severe mucocutaneous reactions, and death. Although neurotoxicity associated with AS has been reported in animals, there is currently no evidence of such toxicity in humans.5-8

### 10.3. Compensation:

The patients/patient’s families will receive reimbursement for transportation costs to and from the clinic. In addition, all clinic visits, antimalarial medication, and the evaluation and treatment for some routine medical problems encountered during follow-up will be provided free of charge. Medical care that the patient receives which is unrelated to malaria will remain the primary responsibility of the patient, parent or guardian, although routine medical problems will generally be managed by the study at no cost to the patient.

### 10.4. Consent procedures:

All screening interviews will be conducted in the native language of the patients by the study personnel (with a translator if necessary). Consent forms will be provided to the patients/ parents or (guardians) for their review. The study clinicians at the clinic will seek formal consent. The patients / parents or (guardians) will be asked to sign consent to participate in a research study. The informed consent will describe the purpose of the study, the procedures to be followed, and the risks and benefits of participation). If the patient, parent or (guardian) is unable to read or write, their fingerprint will be used in substitute for a signature, and a signature from a witness to the informed consent discussion will be obtained. The patients / parents or (guardians) will be informed that the participation in the study is completely voluntary and that they may withdraw from the study at any time.

### 12.0 TIMETABLE

# Table 1. Timetable for Study Activities

|  | **2002** | **2003** | **2004** |
| --- | --- | --- | --- |
| **JFMAMJJASOND** | **JFMAMJJASOND** | **JFMAMJJASOND** |
| **Finalization/approval of study protocol** | XXXXX |  |  |
| Database design | XXX |  |  |
| **Personnel training** | XXX |  |  |
| **Pilot study** | XXX |  |  |
| **Recruitment** | XXXXXX | XXXXXXXXXXXX | XXXXXXXXX |
| **Follow-up** | XXXXXX | XXXXXXXXXXXX | XXXXXXXXX |
| **Data entry/analysis** | XXXXXX | XXXXXXXXXXXX | XXXXXXXXX |
| **Manuscript preparation** |  | XXXXXXXXXXXX | XXXXXXXXXXXX |

# **Target population**

Patients > 6 months with uncomplicated malaria

Living in Sentinel site health center catchment area

**Excluded**

Refer back to OPD for appropriate treatment

Re-assign study number to next study subject

### Appendix 1: Participant Selection and Enrollment

# **Available population**

Patients > 6 months presenting to OPD with symptoms positive screening thick blood smear **(2000/ul – 200,000/ul)**

## Yes

## Yes

## Yes

## No

## No

## No

## No

Day 1

Meet final inclusion criteria?

1. *P. falciparum* monoinfection
2. Parasite density > 2000/ul and < 200,000/ul (Giemsa-stained thick smear)

Excluded on Day 1

Treat and follow-up appropriately

Do **not** re-assign study or treatment number

**Continue with scheduled follow-up**

### No

### Yes

**Screening and recruitment**

Complete screening form

**Informed consent process**

Study number assigned

**Initial enrollment**

Complete Enrollment and CRFs

Perform baseline clinical evaluations

**Randomization and Treatment Allocation**

Treatment number and code selected on basis of subject’s age

Study medication administered by nurse

**Completion of Day 0 visit**

Baseline laboratory evaluations performed

Scheduled for follow-up on Days 1, 2, 3, 7, 14, 21, 28

## Yes

**Persistent vomiting on Day 0**

Re-assign Treatment Number

### APPENDIX 2. CRITICAL STEPS.

Day 1.

Evaluate patient and complete Case Record Form. Record temperature and fever history

Administer study medications (DOT)

Thick smear if severe disease/danger signs

Day 2.

Evaluate patient and complete Case Record Form. Record temperature and fever history, administer study medications (DOT)

Thick smear if severe disease/danger signs or temperature > 37.5 0 C Collect thick blood smear and filter paper sample

Day 3.

Evaluate patient and complete Case Record Form. Record temperature and fever history Collect thick blood smear and filter paper sample

Day 7, 14, 21. Evaluate patient and complete Case Record Form. Record temperature and fever history, collect thick blood smear and filter paper sample

Any Unscheduled Day.

Evaluate patient and complete Case Record Form. Record temperature and fever history. Collect thick blood smear with filter paper sample.

**Parasitaemia > day 0 and**

**Temperature > 37.50 C.**

**ETF**

Treat with quinine.

**Severe disease or danger signs**

Urgent reading of thick blood smear

**Temperature**

**> 37.50C** **with parasitaemia**

**Parasite count >25% Day 0 count.**

**ETF**

Treat with quinine

Day 28.

Evaluate patient and complete Case Record Form. Record temperature and fever history, collect thick blood smear and filter paper sample.

If there is

**Severe disease or danger signs**

**Temp > 37.5C**

**3. History of fever in**  **the past 24 hours.**

Collect thin blood smear.

Urgent reading of thick blood and thin blood smear

**Negative**

Assess for DDx

Continue study Rx

Refer for care?

**Negative**

Assess for DDx

Cont. study Rx

Refer for care?

**Positive blood smear**

**ETF**

Rx with quinine

Refer for care?

**Positive blood smear**

**LTF**

Rx with quinine

Refer for care?

**ACR**

No parasitaemia on day 28 irrespective of fever.

Temperature < 37.50C and no history of fever in the last 24 hours irrespective of parasitaemia.

# Day 2 > Day 0

## ETF

Rx with quinine

Refer for care?

# Day 2 < Day 0

Assess for DDx

Cont. study Rx

Refer for care?

# Yes

## ETF

Rx with quinine

'

### APPENDIX 3. OUTCOME CLASSIFICATION

### Clinical Outcome Classification System

| ACR (Adequate Clinical Response)   - Absence of parasitemia on Day 28, without previously meeting criteria for ETF or LTF - Temperature < 37.5C (Axillary) and no history of fever in last 24 hours on day 28 irrespective of the presence of parasitemia, without previously meeting any of the criteria of ETF or LTF |
| --- |
| ETF (Early Treatment Failure): Days 0, 1, 2, and 3  - Development of danger signs or severe malaria on Days 0-3 in the presence of parasitemia - Parasitemia on Day 2 higher than Day 0 count irrespective of temperature - Temperature > 37.5C (Axillary) on Day 3 in presence of parasitemia - Parasitemia on Day 3 > 25% Day 0 count |
| LTF (Late Treatment Failure): Days 4 To 28  - Development of danger signs or severe malaria on Days 4 to 28 in the presence of parasitemia, without previously meeting any of the criteria of ETF. - Temperature > 37.5C (Axillary) or history of fever in last 24 hours on Days 4 to 28 in the presence of parasitemia, without previously meeting any of the criteria of ETF. |

# Parasitological Outcome Classification System

| RIII   - Severe malaria or danger signs on Day 1 or 2 with parasite count > 25% of Day 0 - Temperature > 37.5C (Axilary) on Day 2 with parasite count > 100% of Day 0 - Parasite count on Day 3 > 25% Day 0 count (with or without fever) |
| --- |
| RII  - Severe malaria or danger signs on Day 1 or 2 with parasite density < 25% of Day 0 - Temperature > 37.5C (A), 38.0C (T) on Day 3 with parasite density < 25% of Day 0 - Parasitemia on Day 3 < 25% on Day 0, parasites present on Days 4-7 |
| RIParasitemia on Day 3 < 25% on Day 0, no parasites on Day 7, parasites present on Days 8-28. |
| **S** Parasitemia on Day 3 < 25% on Day 0, no parasites on Days 7-28 |

**New WHO guidelines for assessing response to treatment (2002)**

| ETF (Early Treatment Failure): Days 0, 1, 2, and 3 |
| --- |
| Development of danger signs or severe malaria on Days 0-3 in the presence of parasitemia |
| Parasitemia on Day 2 higher than on Day 0, irrespective of temperature |
| Parasitemia on Day 3 with temperature > 37.5C (axillary) |
| Parasitemia on Day 3 > 25% of count on Day 0 |
| LCF (Late Clinical Failure): Days 4 To 28 |
| Development of danger signs or severe malaria after Day 3 in the presence of parasitemia, without previously meeting any of the criteria of early treatment failure |
| Temperature > 37.5C (axillary), or history of fever in past 24 hours, on Days 4 to 28 in the presence of parasitemia, without previously meeting any of the criteria of early treatment failure |
| LPF (Late Parasitological Failure): Days 7 To 28 |
| Presence of parasitemia on any day from Day 7 to Day 28, and temperature < 37.5C (axillary), without previously meeting any of the criteria of early or late treatment failure |
| **ACPR (Adequate Clinical and Parasitological Response)** |
| Absence of parasitemia on Day 28, irrespective of temperature, without previously meeting any of the criteria of early or late treatment failure |

### APPENDIX 4. WEIGHT-BASED ADMINISTRATION OF STUDY MEDICATIONS

**Weight-Based Administration of Study Medications (2-arm study)**

| **Weight (kg)** | **Amodiaquine (AQ)**  **200 mg tabs** | | | **Chloroquine (CQ)**  **250 mg tabs** | | | **SP (500mg/**  **25 mg)** |
| --- | --- | --- | --- | --- | --- | --- | --- |
|  | **Day 0** | **Day 1** | **Day 2** | **Day 0** | **Day 1** | **Day 2** | **Day 0** |
| 5 | ¼ | ¼ | ¼ | ¼ | ¼ | ¼ | ¼ |
| 6 | ¼ | ¼ | ¼ | ½ | ¼ | ¼ | ¼ |
| 7 | ¼ | ¼ | ¼ | ½ | ½ | ¼ | ¼ |
| 8 | ½ | ¼ | ¼ | ½ | ½ | ½ | ½ |
| 9 | ½ | ¼ | ¼ | ½ | ½ | ½ | ½ |
| 10 | ½ | ½ | ¼ | ¾ | ½ | ½ | ½ |
| 11 | ½ | ½ | ¼ | ¾ | ¾ | ½ | ½ |
| 12 | ½ | ½ | ½ | ¾ | ¾ | ½ | ½ |
| 13 | ½ | ½ | ½ | 1 | ¾ | ½ | ¾ |
| 14 | ¾ | ½ | ½ | 1 | 1 | ½ | ¾ |
| 15 | ¾ | ½ | ½ | 1 | 1 | ½ | ¾ |
| 16 | ¾ | ¾ | ½ | 1 | 1 | ¾ | ¾ |
| 17 | ¾ | ¾ | ½ | 1 | 1 | 1 | ¾ |
| 18 | 1 | ¾ | ½ | 1 | 1 | 1 | ¾ |
| 19 | 1 | ¾ | ½ | 1 ¼ | 1 | 1 | 1 |
| 20 | 1 | 1 | ½ | 1 ¼ | 1 ¼ | 1 | 1 |
| 21 | 1 | 1 | ½ | 1 ¼ | 1 ¼ | 1 | 1 |
| 22 | 1 ¼ | 1 | ½ | 1 ½ | 1 ½ | ¾ | 1 |
| 23 | 1 ¼ | 1 | ½ | 1 ½ | 1 ½ | 1 | 1 ¼ |
| 24 | 1 ¼ | 1 ¼ | ½ | 1 ½ | 1 ½ | 1 | 1 ¼ |
| 25 | 1 ¼ | 1 ¼ | ½ | 1 ½ | 1 ½ | 1 ¼ | 1 ¼ |
| 26-27 | 1 ¼ | 1 | 1 | 1 ½ | 1 ½ | 1 ¼ | 1 ½ |
| 28 | 1 ¼ | 1 ¼ | 1 | 2 | 1 ½ | 1 ½ | 1 ½ |
| 29-31 | 1 ¼ | 1 ¼ | 1 | 2 | 2 | 1 | 1 ½ |
| 32 | 1 ½ | 1 ½ | 1 | 2 | 2 | 1 ½ | 1 ½ |
| 33 | 1 ½ | 1 ½ | 1 | 2 | 2 | 1 ½ | 1 ½ |
| 34-35 | 1 ½ | 1 ½ | 1 ¼ | 2 | 2 | 2 | 1 ½ |
| 36-37 | 1 ½ | 1 ½ | 1 ¼ | 2 | 2 | 2 | 1 ½ |
| 38 | 2 | 1 ½ | 1 ¼ | 2 | 2 | 2 | 2 |
| 39 | 2 | 1 ½ | 1 ¼ | 2 | 2 | 2 | 2 |
| 40-43 | 2 | 2 | 1 | 2 ½ | 2 ½ | 1 ½ | 2 |
| 44-47 | 2 | 2 | 1 ½ | 3 | 3 | 2 | 2 ½ |
| 48-49 | 2 | 2 | 2 | 3 | 3 | 2 | 2 ½ |
| 50-59 | 2 ½ | 2 | 2 | 4 | 4 | 2 | 2 ¾ |
| >60 | 3 | 3 | 1 ½ | 4 | 4 | 2 | 3 |

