### 4.4. Treatment allocation and masking:

On the day of enrolment, study participants will undergo baseline evaluations and be assigned a study number by the clinicians. Patients will then be referred to the study nurse who will be responsible for the treatment group assignment and allocation of the study medications. The study nurse will note the patient’s age and select the next available treatment number and corresponding assigned treatment. The study nurse will record directly onto the randomization list the date and time of treatment assignment and study number. Once a month, a copy of the updated randomization list will be placed by the study nurse into sealed envelopes and delivered to the administrative office in Kampala where they will be stored securely. The original randomization list will be crosschecked to assure adherence to the randomisation code. Initial studies will involve one of the two following treatment comparison designs:

1. Two-arm study – CQ/SP vs. AQ/SP
2. Three-arm study - CQ/SP vs. AQ/SP vs. AQ/AS

Sentinel sites with previously identified low levels of drug resistance and/or lower-level capacity for the conduct of complex studies will be chosen for the two-arm study. Sentinel sites with previously identified higher levels of drug resistance and greater capacity will be chosen for the three-arm study.

The nurse shall administer study medications according to weight-based guidelines (Appendix 4). Study medications will not be identical in appearance or taste, however other procedures will be followed in an attempt to mask the patients to their treatment. Patients will not be informed of their treatment regimen and identical dosing regimens will be used in all the treatment arms. In studies where AS/AQ shall be compared with CQ/SP and AQ/SP, patients assigned to CQ/SP and AQ/SP shall be given a placebo (lactose tablets) on day 1 and day 2 in the same amount as AS. Administration of study medications will be directly observed. Any patient who vomits the medication within 30 minutes of administration of the drugs will be retreated with a second dose. If the patient vomits repeatedly on Day 0, they shall be excluded. If the patient vomits repeatedly on Day 1 or 2 and is unable to retain the dose of the study medication, the patient will be classified as a treatment failure and referred for appropriate care with parental antimalarial medication.

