### 6.3.2 Study drug dosing schedule:

| **Treatment Groups** | **Medications** | **Day 0** | **Day 1** | **Day 2** |
| --- | --- | --- | --- | --- |
| CQ/SP | CQ | 10 mg/kg | 10 mg/kg | 5 mg/kg |
| SP | 25 mg/kg sulfa component | Placebo if 3-arm  study | Placebo if 3-arm  study |
| AQ/SP | AQ | 10 mg/kg | 10 mg/kg | 5 mg/kg |
| SP | 25 mg/kg sulfa component | Placebo if 3-arm  study | Placebo if 3-arm  study |
| AS/AQ | AS | 4 mg/kg | 4 mg/kg | 4 mg/kg |
| AQ | 10 mg/kg | 10 mg/kg | 5 mg/kg |

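### Section 6.3.2 states amodiaquine 10/10/5 mg/kg by day, but the Appendix 4 tablet counts deliver about 25 mg/kg over three days without keeping that daily split

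*Protocol*

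**What the plan says.** The dosing schedule in section 6.3.2 gives "AQ/SP | AQ | 10 mg/kg | 10 mg/kg | 5 mg/kg" for Days 0, 1 and 2, and the same AQ doses in the AS/AQ arm. Section 6.3.1 lists AQ as a 200 mg tablet. Section 4.4 makes the appendix the working instruction: "The nurse shall administer study medications according to weight-based guidelines (Appendix 4").

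Appendix 4 lists tablets by weight in quarter-tablet steps. In the 2-arm table each row gives AQ on Days 0, 1 and 2, then chloroquine on the same days, then SP on Day 0. The AQ columns of the 3-arm table are identical. These rows matter here:
- the last row before the split changes: "25 | 1 ¼ | 1 ¼ | ½ | 1 ½ | 1 ½ | 1 ¼ | 1 ¼"
- the row where Day 1 drops and Day 2 doubles: "26-27 | 1 ¼ | 1 | 1 | 1 ½ | 1 ½ | 1 ¼ | 1 ½"
- a row with Day 1 well below target: "39 | 2 | 1 ½ | 1 ¼ | 2 | 2 | 2 | 2"
- a row that keeps the stated split: "40-43 | 2 | 2 | 1 | 2 ½ | 2 ½ | 1 ½ | 2"
- a row with three equal days: "48-49 | 2 | 2 | 2 | 3 | 3 | 2 | 2 ½"
- the widest weight band: "50-59 | 2 ½ | 2 | 2 | 4 | 4 | 2 | 2 ¾"

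The protocol does not say that only the course total is to be matched.

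**The concern.** The two statements of the AQ dose should agree to within tablet rounding, and over much of the weight range they do not. From 25 to 26 kg, Day 1 drops from 1¼ tablets to 1 while Day 2 doubles from ½ to 1. At 48-49 kg the three days are equal. A fixed mg/kg dose, rounded day by day, cannot fall as weight rises.

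What is at stake is the description of the tested regimen. Section 2.2 says the data go directly to the Ministry of Health for drug policy. A report that took 10/10/5 from 6.3.2 would, at the affected weights, generally describe a higher Day 1 dose and a lower Day 2 dose than patients received.

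**Working it through.** **Inputs.** Targets of 10, 10 and 5 mg/kg (6.3.2), the 200 mg tablet (6.3.1) and the AQ counts in all 35 rows of Appendix 4. I took every whole kilogram from 5 to 59, plus 60 kg for the top row, which makes 56 weights.

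**Formulas.** For weight w in kg:
- target tablets = 10w/200 on Days 0 and 1, and 5w/200 on Day 2
- delivered dose in mg/kg = tablets × 200 / w
- miss = printed tablets − target tablets

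Rounding a single day to the nearest quarter tablet explains a miss of at most 0.125 tablet. I counted a weight when any day missed by 0.25 tablet or more.

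**Rows that reproduce the stated dose.** At 40 kg the target is 2.0/2.0/1.0 and the table prints 2/2/1. At 60 kg the target is 3.0/3.0/1.5 and the table prints 3/3/1½. Both are exactly 10/10/5.

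**Rows that do not.**

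| Weight | Target tablets | Printed tablets | Delivered mg/kg | Total mg/kg |
|---|---|---|---|---|
| 26 kg | 1.30/1.30/0.65 | 1.25/1/1 | 9.6/7.7/7.7 | 25.0 |
| 39 kg | 1.95/1.95/0.975 | 2/1.5/1.25 | 10.3/7.7/6.4 | 24.4 |
| 48 kg | 2.40/2.40/1.20 | 2/2/2 | 8.3/8.3/8.3 | 25.0 |
| 59 kg | 2.95/2.95/1.475 | 2.5/2/2 | 8.5/6.8/6.8 | 22.0 |

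For 26 kg on Day 1: 1 × 200 / 26 = 7.7 mg/kg, and the miss is 1 − 1.30 = −0.30 tablet.

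**Count.** At least one day misses by a quarter tablet or more at 15, 26-31, 34-39 and 44-59 kg. That is 1 + 6 + 6 + 16 = 29 of 56 weights, in 11 of 35 rows. By day the misses number 15, 25 and 27 on Days 0, 1 and 2. On the missed days the delivered doses are:
- Day 0: 8.1-9.1 mg/kg against 10 (9-19% low)
- Day 1: 6.7-8.9 mg/kg against 10 (11-33% low)
- Day 2: 6.4-8.3 mg/kg against 5 (28-67% high)

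If only misses strictly above 0.25 tablet count, 15 and 30 kg drop out and 27 weights remain.

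**Below 26 kg.** Misses above 0.125 tablet, so beyond single-day rounding, occur at 8, 9, 12-15, 18, 19, 22 and 23 kg. That is 10 of the 21 weights from 5 to 25 kg, and 15 kg is the only one that reaches a quarter tablet.

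**Course total.** The three-day total is within 10% of 25 mg/kg at 51 of 56 weights. The exceptions are 5 kg (30.0), 7 kg (21.4), 9 kg (22.2), 58 kg (22.4) and 59 kg (22.0). It is exactly 25.0 at every even weight from 6 to 28 kg, and at 32, 34, 38, 40, 44, 48 and 60 kg. For example, at 26 kg: (1.25 + 1 + 1) × 200 / 26 = 25.0.

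**The case against.** The strongest reply is that Appendix 4 follows a visible rule: it fits a 25 mg/kg course to quarter tablets and lets the split vary. The totals support this. The counts that fall with weight do not mark an AQ error either, because chloroquine does the same on Day 2: from 1 to ¾ tablet at 21 to 22 kg, from 1½ to 1 at 28 to 29 kg, and from 2 to 1½ at 39 to 40 kg. That stands. A reader might infer that the AQ table was miscounted, but the documents do not support it; the falls show only that days were not rounded one by one.

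It is also fair that a cut-off in tablets flags heavier patients more readily. In mg/kg, some of the largest departures are at low weights that are not among the 29: Day 1 is 5.6 mg/kg at 9 kg (44% low) and Day 2 is 10.0 mg/kg at 5 kg (100% high). So 26 kg is not a sharp boundary. Ten of the 29 weights also come from the single 50-59 kg row.

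The nurse's instruction is unambiguous, and no endpoint, comparison or sample size changes. None of this makes 6.3.2 correct: it states a daily dose that the governing table does not deliver, and no rule in the protocol reconciles the two.

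**Conclusion.** The point holds as a misstated daily schedule, at minor severity. Appendix 4 delivers roughly the intended 25 mg/kg course, but at 29 of 56 whole-kilogram weights it misses at least one stated daily dose by a quarter tablet or more. Smaller departures beyond rounding occur at lower weights.

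Three stronger readings are not supported:
- **Systematic underdosing.** The total is 22.0-26.0 mg/kg at the 29 weights.
- **Bias between the AQ arms.** The AQ counts are the same in both.
- **Most patients affected.** The protocol gives no weight distribution, so a count of weights says nothing about the share of patients.

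The count assumes whole-kilogram weights and the top row taken at 60 kg; without that row it is 29 of 55. That the table was designed on the course total is inferred from the pattern of totals, since the protocol does not say so.

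**What to change.** Restate the AQ entries in section 6.3.2 as about 25 mg/kg over three days, nominally 10/10/5, given as the Appendix 4 tablet counts. Add the daily range those counts deliver at 26-59 kg: Day 0 8.1-10.5, Day 1 6.8-10.0 and Day 2 4.7-8.3 mg/kg. Describe the regimen the same way in reports. This costs one sentence and adds no patients, visits or analyses.

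Moving rows closer to 10/10/5 is optional and is for the sponsor's pharmacist to decide. At 26-27 kg, for instance, 1¼/1¼/¾ keeps the 3¼-tablet total and brings the misses at 26 kg to −0.05/−0.05/+0.10 tablet. Re-splitting at the printed totals would not remove the need for the sentence: 30, 31, 50 and 55-59 kg would still be off by a quarter tablet or more, and some rows would need more tablet cutting.
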